### Randomisation

Once consent has been obtained and all entry criteria are met with no exclusions, the infant is randomised by the OPTIMIST Treatment Team, after handover of care from the treating clinicians. Enrolled infants are randomised into “surfactant via MIST” and “standard care” (sham treatment) groups, with an allocation ratio of 1:1, using a web-based randomisation procedure that requires confirmation of eligibility criteria and consent before revealing the randomly determined allocation. The randomisation is in randomly permuted blocks of variable length, stratified by study centre, and by gestational age. For the OPTIMIST-A trial there are two gestational age strata (25–26 weeks and 27–28 weeks). Twins and higher order multiples are randomised independently. Infants who are unstable and in need of immediate intubation should not be randomised, even if consent has been obtained; such infants will not be considered to have been enrolled.

### Masking

In order to mask the group allocation from the treating clinicians, an OPTIMIST Treatment Team is mobilised to perform the randomisation and intervention. This team consists of a neonatologist, senior neonatal trainee or neonatal nurse practitioner, and a neonatal nurse, none of whom are currently involved in the infant’s care. Their role is to obtain the randomisation, and then within 1 hour, after screening the infant as effectively as possible from the treating clinicians, to administer the intervention (surfactant via MIST or sham treatment) in accordance with the randomised allocation. Their activities, including removal of surfactant from the medication refrigerator, movement and speech within the screened space, and manipulation of the infant, should be such that the treating clinicians cannot discern which intervention is received. All treating clinicians are made aware that the OPTIMIST Treatment Team will be concealing treatment allocation by performing a sham procedure on those infants randomised to standard care. The time taken to perform the intervention should be the same regardless of treatment allocation, and the infant is returned to the pre-intervention CPAP settings prior to removing the screens. A survey of clinical staff is being conducted after each OPTIMIST intervention in order to assess the success of masking.

Members of OPTIMIST Treatment Teams at all institutions undertake not to reveal the allocation group of randomised infants.

### Intervention

The intervention is performed in the NICU of participating centres. Prior to intervention, all neonates must be stable on CPAP delivered by prongs or mask. An intravenous cannula should be *in situ*. It is desirable that a blood gas analysis (arterial or capillary) is performed before intervention, although this is not mandatory. A chest X-ray is recommended to confirm the diagnosis of RDS, and to exclude other causes of respiratory distress.

Having been briefed on the current condition of the infant, the OPTIMIST Treatment Team screens the infant from treating clinicians as completely as possible. The infant is then randomised, and the allocated intervention carried out as soon as possible (maximum 1 h after randomisation). Pre-intervention observations are recorded. The Treatment Team takes a labelled box containing full or empty surfactant vials from the OPTIMIST canister in the medication refrigerator. This canister must not be accessed by any other person other than the NICU pharmacist responsible for replenishing the stock of surfactant, which is supplied specifically for the study.

### Intervention – surfactant administration via MIST

The following protocol is used for performing MIST:

#### Preparation

1. Prepare the 16G Angiocath by marking a point indicating the desired depth of insertion beyond the vocal cords with a marker pen. The required depth is as follows: 25–26 weeks: 1.5 cm; 27–28 weeks 2.0 cm. Some investigators may find that tracheal catheterisation is facilitated by fashioning a slight anterior curve in the catheter.

2. Draw up the surfactant (Curosurf™, Chiesi Farmaceutici, Parma, Italy) in a 3 or 5 mL syringe. The surfactant dose is 200 mg/kg (2.5 mL/kg). Draw up an additional 0.5 mL of air into the syringe, taking account of the dead volume of the instillation catheter (~0.3 mL).

3. Optional: administer atropine 20 μg/kg intravenously.

4. Disconnect standard monitors and connect the infant to the OPTIMIST oximeter (supplied to each centre)

5. The infant can be swaddled and oral sucrose administered as part of standard procedural nursing care.

#### Performing MIST

1. Position the infant as for a standard intubation procedure.

2. If possible, the laryngoscopy and tracheal cannulation should be performed with the CPAP prongs remaining *in situ*. An alternative which may improve the view of the vocal cords is to remove the CPAP prongs and apply CPAP by mask until the laryngoscopy commences.

3. Perform direct laryngoscopy using a standard laryngoscope and blade. Alternatively, use the Glidescope Cobalt AVL video laryngoscope and size 0 stat.

4. Insert the surfactant instillation catheter through the vocal cords to the desired depth, and hold it in position at the lips. The laryngoscope should then be removed.

5. Connect the surfactant syringe to the catheter hub, and instil the surfactant in 2–4 boluses over 15–30 seconds.

6. Once the surfactant is instilled, immediately remove the instillation catheter and apply CPAP by prongs or facemask.

7. If on the first attempt catheterisation of the trachea is not possible within 20–30 seconds, remove the laryngoscope, allow recovery on CPAP as required, and then attempt tracheal catheterisation once again. The maximum number of catheterisation attempts should be 3, after which the procedure should be abandoned.

#### After MIST

1. Once heart rate, SpO_2_ and respiratory effort are close to baseline values, restore the infant to their previous position, and re-establish CPAP with the same device and settings as prior to surfactant instillation.

2. Details of the procedure are recorded on a data form specifically related to the intervention. This form is then removed from the bedside by the Treatment Team, and sent to the OPTIMIST Data Management Centre in electronic format. A copy of the form should be placed in locked cabinet away from the clinical area.

3. Observations are recorded 5 minutes post-intervention, after which the OPTIMIST oximeter is disconnected and normal monitoring resumed.

4. All items that could reveal the treatment allocation to the treating clinicians should be cleared from the bedside.

Because of the novelty of the MIST technique, OPTIMIST Investigators are given the opportunity to practise the technique on an intubation mannequin during an OPTIMIST training workshop. Experience from the feasibility studies at RHH Hobart and RWH Melbourne indicates that neonatologists and neonatal fellows are highly likely to succeed in tracheal catheterisation from the outset, although two attempts at catheterisation may be required until familiarity with the technique is gained.

### Intervention – standard care (sham MIST procedure)

The following protocol is used in the standard care group:

1. Position the infant as for a standard intubation procedure. This is the only actual intervention for babies randomised to standard care. CPAP is not interrupted at any time in this group. The OPTIMIST oximeter is used and standard monitoring disconnected as for the MIST procedure.

2. Simulate the MIST procedure in terms of time taken and movement and communication within the screened area.

3. After the procedure, restore the infant to their previous position, and ensure the CPAP settings are the same as prior to the sham procedure.

4. Record the time of the sham intervention on the OPTIMIST Intervention Form, remove the form from the bedside, and send to the Data Management Centre, retaining a copy, exactly as described for the MIST procedure above.

### Management immediately after MIST

Once the MIST procedure or sham procedure is completed, the screens around the infant are removed, and care of the infant returned to the treating clinicians. For all infants, attention is drawn to the possible need to reduce the FiO_2_ so as to keep SpO_2_ in the target range. An entry is made on the drug chart to indicate the timing of the OPTIMIST study intervention. A card is placed at the bedside indicating that the infant has been enrolled in the trial, and displaying the intubation criteria. Post-intervention observations are recorded by the treating clinicians at 4 hours.

### Post-MIST investigations

A blood gas analysis (arterial or capillary) should be performed at 4 hours post-intervention, or earlier if clinically indicated.

### Post-intervention management

Other than the requirement to adhere to intubation criteria in the first week, and in some cases perform a room air trial at 36 weeks corrected gestation, management of enrolled infants after intervention is at the discretion of the clinical team. Titration of CPAP pressure according to work of breathing and oxygen requirement is encouraged. Maximum acceptable CPAP pressure is 8 cm H_2_O. NIPPV (bi-level CPAP) is allowable. Adjustment of FiO_2_ should be so as to target an SpO_2_ range appropriate for gestation and post-natal age. Prophylactic caffeine therapy would be expected in all infants [41].

#### Criteria for intubation

Infants should be intubated and ventilated if, and only if, they fulfil any of the following criteria:

1. FiO_2_ ≥ 0.45. To qualify for intubation, the FiO_2_ must be sustained at intubation level for at least 15 minutes, and all other aspects of CPAP management must have been optimised (including prong size and position, and minimisation of CPAP pressure leak).

2. Apnoea unresponsive to caffeine therapy and stimulation, which is either frequent (6 episodes in 6 hours requiring vigorous stimulation), or severe (more than one episode requiring positive pressure ventilation)

3. Persistent respiratory acidosis with pH < 7.20 and PCO_2_ > 65 mm Hg on two blood gas samples at least 30 minutes apart, or metabolic acidosis refractory to treatment

4. Need for an anaesthetic or an intervention requiring intubation

Note that these criteria apply only during the first week of life, and only for the first episode of intubation.

Once intubated, surfactant therapy can be given, at the discretion of the treating clinicians. There is no likelihood of harm if a further dose of surfactant is given less than 6 hours after surfactant administration via MIST. Thus the treating clinicians remain masked in this circumstance.

#### Assessment of BPD at 36 weeks corrected gestational age

Incidence of BPD based on oxygen requirement at 36 weeks corrected gestational age is variable within units in the Australian and New Zealand Neonatal Network (ANZNN), certainly in part due to variability in approach to oxygen therapy amongst units. Given the primacy of BPD as an outcome in the OPTIMIST-A trial, a standardised approach to its recognition has been incorporated into the trial design, based around the National Institute of Child Health and Disease consensus panel definition of “physiological BPD” [42]. On or shortly after 36 weeks 0 days corrected gestation, infants not requiring respiratory support (intubation/CPAP/HFNC ≥ 2 L/min) but receiving oxygen therapy with an FiO_2_ of less than 0.30 have a trial of room air. For infants on nasal cannula oxygen the “effective FiO_2_” is determined using the Benaron-Benitz formula [43], currently available as on online calculator (http://pub.emmes.com/study/rop/stop-js.html). Those with an FiO_2_ < 0.30 have an air trial involving stepwise FiO_2_ reductions 5 minutes apart until either room air is being administered or SpO_2_ is no longer within the target range. Based on current evidence, the minimum acceptable SpO_2_ reading for this trial is 91% [44]. A successful room air trial is defined as SpO_2_ readings ≥91% for 30 minutes in room air with nasal prongs removed [42]. Oxygen therapy can thereafter be reinstituted if deemed necessary by the treating clinicians.

Infants receiving HFNC therapy with FiO_2_ 0.21 and flow < 2 L/min also have a room air trial as above with the nasal prongs removed.

Infants requiring respiratory support, and those failing the room air trial, are deemed to have physiological BPD. BPD using the standard (clinical) definition is diagnosed if oxygen and/or respiratory support (intubation/CPAP/HFNC ≥2 L/min) is being administered for any portion of the day at 36 weeks and 0 days corrected gestational age.

Severity of BPD is categorised according to the consensus definitions [42]:

Mild BPD: need for oxygen at 28 days but not at 36 weeks corrected gestation.

Moderate BPD: need for oxygen at 28 days and continued oxygen requirement at 36 weeks (confirmed by room air trial), with FiO_2_ < 0.30.

Severe BPD: need for oxygen at 28 days, and at 36 weeks an oxygen requirement with FiO_2_ ≥ 0.30 and/or need for positive pressure support (intubation, CPAP, HFNC ≥2 L/min).

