#### Secondary outcomes

A range of standard clinical outcomes pertaining to the first hospitalisation are being ascertained in trial participants. These are shown in Table 1. Additionally, data are being collected in the intervention group relating to the applicability and safety of the Hobart method (Table 2). For this purpose, data from the study oximeter are used alongside data recorded manually by the Treatment Team. Finally, longer term outcomes are being evaluated at two years corrected age as part of the OPTIMIST-A follow-up study. This study will have its own protocol and funding stream. Selected outcomes from this study are shown in Table 3.

**Table 1 T1:** Clinical outcomes during first hospitalisation

Physiological BPD [42]	Duration of intubation (all episodes)
Clinical BPD (oxygen or positive pressure support at 36 weeks corrected gestation) [45]	Duration of CPAP/NIPPV (all episodes)
Mild/moderate/severe BPD [45]	Duration of intubation and CPAP
Death	Duration of HFNC, minimum flow rate 2 L/min
Death or BPD (clinical definition)	Duration of respiratory support
Intraventricular haemorrhage (IVH) (all grades)	Duration of oxygen therapy
IVH grades III and IV [46]	Requirement for oxygen at home
Cystic periventricular leukomalacia	Length of stay in intensive care
Retinopathy of prematurity (ROP) > stage II	Length of hospital stay
Major morbidity (any of IVH grade III or IV, periventricular leukomalacia, ROP > stage II, physiological BPD) [47]	Total hospital billings
Death or major morbidity	Calculated cost of hospitalisation
NEC (Modified Bell stage 2 or greater) [48]	Pneumothorax requiring drainage
NEC or spontaneous intestinal perforation requiring surgery	Pulmonary haemorrhage
Requirement for intubation < 72 h	Patent ductus arteriosus (PDA) requiring anti-prostaglandin therapy
Requirement for intubation at any time	PDA requiring ligation
Need for additional surfactant therapy	Late onset sepsis (positive bacterial or fungal culture from a normally sterile site)
Overall number of surfactant doses (including that given by MIST)	Time to regain birth weight

**Table 2 T2:** Applicability and safety outcomes in infants randomised to receive surfactant via the Hobart method

Incidence of successful surfactant administration via MIST	Duration of hypoxaemia (SpO_2_ < 80%)
Number of catheterisation attempts	Requirement for, and duration of, positive pressure ventilation by mask

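### The BPD severity grades give one kind of infant two grades and give no grade to infants with physiological BPD who did not need oxygen at 28 days

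*Protocol article*

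**What the plan says.** The Protocol article, under Assessment of BPD at 36 weeks corrected gestational age, sets out two classifications.

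The first is physiological BPD, which with death makes up the primary outcome: "Infants requiring respiratory support, and those failing the room air trial, are deemed to have physiological BPD". The air trial is for infants who are off respiratory support "but receiving oxygen therapy with an FiO_2_ of less than 0.30 have a trial of room air", and for those on HFNC below 2 L/min in FiO2 0.21. Day 28 plays no part in this rule.

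The second is the severity grading, attributed there to a cited consensus definition:

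- Mild: "Mild BPD: need for oxygen at 28 days but not at 36 weeks corrected gestation".
- Moderate: "Moderate BPD: need for oxygen at 28 days and continued oxygen requirement at 36 weeks (confirmed by room air trial", with FiO2 below 0.30.
- Severe: "Severe BPD: need for oxygen at 28 days, and at 36 weeks an oxygen requirement" at FiO2 0.30 or above "and/or need for positive pressure support (intubation, CPAP, HFNC ≥2 L/min".

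No order of precedence among the grades is given. Table 1 lists the three-level grading as a secondary outcome, separately from physiological BPD and clinical BPD.

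**The concern.** Two features of the grading do not fit the physiological rule in the same section. First, mild looks only at oxygen at 36 weeks and ignores pressure support, whereas severe accepts pressure support without any oxygen requirement. The lowest and highest grades can therefore both describe one infant. Second, every grade depends on oxygen at 28 days, a condition that physiological BPD does not have. Some infants who count as events in the primary analysis therefore cannot be placed on the severity scale.

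What is at stake is the readability of one listed secondary outcome. As written, moderate plus severe need not equal physiological BPD, and mild can contain infants who are positive for the primary outcome. The infants concerned are foreseeable: enrolment is of infants on CPAP or NIPPV, and the section itself provides for CPAP and HFNC at 36 weeks, including low-flow HFNC in FiO2 0.21.

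**Working it through.** The plan gives no figure on this point to reproduce. The 297 per arm under Sample size concerns the primary outcome and does not depend on the grades. The check is to apply the written rules to every combination.

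**Inputs**, all from the BPD assessment section: oxygen need at 28 days (yes or no); support at 36 weeks (none, HFNC below 2 L/min, or intubation/CPAP/HFNC ≥2 L/min); FiO2 (0.21, 0.22–0.29, ≥0.30); and the air trial result where a trial is held. This gives 12 states at 36 weeks for each 28-day status, 24 in all. Below, off support means no support or HFNC below 2 L/min, and a failed air trial is taken to show an oxygen requirement.

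| Status at 36 weeks (number of states) | Physiological BPD | Grade if oxygen at 28 days | Grade if none at 28 days |
|---|---|---|---|
| Off support, in air, no trial needed (1) | no | mild | none |
| Off support, trial passed (3) | no | mild | none |
| Off support, trial failed (3) | yes | moderate | none |
| Off support, FiO2 ≥0.30, no trial held (2) | not stated | severe | none |
| On support, FiO2 0.21 (1) | yes | **mild and severe** | none |
| On support, FiO2 0.22–0.29 (1) | yes | severe | none |
| On support, FiO2 ≥0.30 (1) | yes | severe | none |

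These are counts of states, not of infants.

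**Overlap.** With oxygen at 28 days, 11 of the 12 states have one grade and 1 has two. Moderate does not overlap with either neighbour: it needs confirmation by an air trial, and infants on support do not have one.

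**Gap.** Without oxygen at 28 days, none of the 12 states has a grade, although 3 + 1 + 1 + 1 = 6 of them are physiological BPD.

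**A third, smaller point.** An infant off support on FiO2 ≥0.30 is graded severe if oxygen was needed at 28 days. The physiological rule names only infants on support and infants who fail the trial, and this infant is neither.

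**Can the effect on the arm comparison be sized?** Settle the overlap as severe and count FiO2 ≥0.30 off support as physiological BPD. Let B be an arm's proportion with physiological BPD and u the share of those infants with no oxygen need at 28 days. Then graded moderate or severe BPD = B × (1 − u). If B is the same in both arms, the spurious difference between arms is B × (difference in u), which is zero when u is the same. The documents give neither B (the 38% is death or BPD combined) nor u in either arm. Any percentage attached to this would only return the values assumed.

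**The case against.** The strongest reply is that the grading is a declared published scale, that its 28-day condition belongs to that scale, and that an article may leave precedence rules to a fuller document. On an ordered scale the natural reading is that the highest grade met applies, and severe expressly names pressure support. The plan also never promises that moderate plus severe will sum to physiological BPD, and this is one line among more than 30 secondary outcomes.

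Part of this stands. A worst-grade-first reading would remove the overlap, and the consensus grading need not be discarded. But that reading is not stated, and it does nothing for infants ungraded at 28 days. The article does not defer the definitions either. It writes out all three beside a physiological rule that they do not fit, in a section meant to standardise the recognition of BPD across units.

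A reader might go further and infer that the 28-day condition would favour MIST by making its BPD look milder. The documents do not support that. Under Clinical experience with the Hobart method, the faster FiO2 weaning covers only the first 72 hours, and it and the shorter oxygen therapy come from comparison with historical controls. Neither shows that MIST infants would more often be on pressure support in air at day 28, and the trial hypothesis expects shorter mechanical respiratory support as well. Infants without oxygen need at 28 days also become ungraded, not mild.

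**Conclusion.** The point holds on the literal wording, within narrow bounds. One state is graded both mild and severe, and every infant with physiological BPD but no oxygen need at 28 days is ungraded. The effect is confined to the secondary severity outcome. Its size and direction in the arm comparison are unknown, because the number of infants in these states cannot be derived from the documents.

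Two wider readings should be resisted. The three grades do not overlap generally: only mild and severe do, in a single state. Nor is the primary outcome put in doubt by the grading, since physiological BPD is determined without it.

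The conclusion assumes that the article's wording is what will be applied. An analysis plan that is not shown may already contain a rule, but the published definitions would still need correcting. This is worth doing because it is a stated rule that misclassifies a foreseeable group and is easily repaired.

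**What to change.** 1. Define mild as oxygen need at 28 days with neither an oxygen requirement nor positive pressure support at 36 weeks. Support in FiO2 0.21 is then severe only, and each infant with oxygen need at 28 days has exactly one grade.
2. Keep the cited consensus grading, and add a second table by arm in which all infants with BPD at 36 weeks are graded on 36-week status alone. Severe is positive pressure support or FiO2 ≥0.30; moderate is a failed air trial with FiO2 below 0.30. Infants without oxygen need at 28 days are then counted.
3. State that an infant off support on FiO2 ≥0.30 at 36 weeks, who has no air trial, counts as physiological BPD. This step is needed: if only infants literally meeting the present physiological rule were regraded, and all others with oxygen at 28 days were called mild, this infant would move from severe to mild.

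With all three changes, for either 28-day status, the second table has 3 moderate states and 2 + 3 = 5 severe states. These 8 are the 6 states already deemed physiological BPD plus the 2 added by step 3, so moderate plus severe equals physiological BPD.

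The cost is a few sentences of definition, one extra table, and a small departure from the consensus wording in that table. The inputs are those the present definitions already use. The source of the grading could be aligned at the same time: it is reference 42 in the assessment section and 45 in Table 1.
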